# THE SAAF STUDY: evaluation of the *Safeguarding Children Assessment and Analysis Framework* (SAAF), compared with management as usual, for improving outcomes for children and young people who have experienced, or are at risk of, maltreatment: study protocol for a randomised controlled trial

**DOI:** 10.1186/1745-6215-15-453

**Published:** 2014-11-20

**Keywords:** Assessment, Decision-making, Child protection, Social work, Child maltreatment, Implementation

## Abstract

**Background:**

Serious case reviews and research studies have indicated weaknesses in risk assessments conducted by child protection social workers. Social workers are adept at gathering information but struggle with analysis and assessment of risk. The Department for Education wants to know if the use of a structured decision-making tool can improve child protection assessments of risk.

**Methods/design:**

This multi-site, cluster-randomised trial will assess the effectiveness of the *Safeguarding Children Assessment and Analysis Framework (SAAF*). This structured decision-making tool aims to improve social workers’ assessments of harm, of future risk and parents’ capacity to change. The comparison is management as usual.

Inclusion criteria: Children’s Services Departments (CSDs) in England willing to make relevant teams available to be randomised, and willing to meet the trial’s training and data collection requirements.

Exclusion criteria: CSDs where there were concerns about performance; where a major organisational restructuring was planned or under way; or where other risk assessment tools were in use.

Six CSDs are participating in this study. Social workers in the experimental arm will receive 2 days training in SAAF together with a range of support materials, and access to limited telephone consultation post-training.

The primary outcome is child maltreatment. This will be assessed using data collected nationally on two key performance indicators: the first is the number of children in a year who have been subject to a second Child Protection Plan (CPP); the second is the number of re-referrals of children because of related concerns about maltreatment.

Secondary outcomes are: i) the quality of assessments judged against a schedule of quality criteria and ii) the relationship between the three assessments required by the structured decision-making tool (level of harm, risk of (re)abuse and prospects for successful intervention).

**Discussion:**

This is the first study to examine the effectiveness of SAAF. It will contribute to a very limited literature on the contribution that structured decision-making tools can make to improving risk assessment and case planning in child protection and on what is involved in their effective implementation.

**Trial registration:**

ISRCTN 45137562 15 July 2014.

## Background

In 2010, [name] was commissioned to chair a review of the child protection system in England. As part of a wide-ranging brief, she was charged with generating ideas about how to improve early intervention, enhance trust in frontline social workers and improve transparency and accountability in child protection. A central question for the review panel was ‘what helps professionals make the best judgments they can to protect a vulnerable child?’ [1, p.6]. The final report [1] highlighted the failure of historical attempts to improve assessment and decision-making via increased regulation, guidance and procedural requirements, rather than by developing and supporting the analytic and decision-making skills of social workers. It therefore recommended moving away from a culture of prescription and compliance (the ‘status quo’) to one that emphasised the importance of professional judgement. Achieving this necessitates ensuring that staff are equipped with the necessary knowledge and skills to exercise sound judgement, and chapter 6 of the *Final Report* addresses these issues in detail, noting the importance of the ‘ability to analyse critically the evidence about a child and family’s circumstances and to make well-evidenced decisions and recommendations, including when a child cannot remain living in their family either as a temporary or permanent arrangement; and skills in achieving some objectivity about what is happening in a child’s life and within their family, and assessing change over time’ (p.96).

There is a wide body of evidence to suggest that social workers are adept at gathering information, but find it challenging to analyse complex bodies of evidence and reach accurate judgement as to whether a child is suffering, or is likely to suffer, significant harm. Some studies have suggested that child protection assessments are ‘only slightly better than guessing’ [2]. Key reasons for poor quality assessments and decision-making are an inability or failure critically to appraise information collected, random errors, and our susceptibility to sources of bias such as ‘observation bias’ (a tendency to see things and people in a particular way, based either on what we are told about them beforehand or on the basis of certain features), ‘cultural relativism’ (the tendency to exercise different standards across different cultures) and the dominance of first impressions. These, and other sources of bias, have consistently been implicated in decision-making, as analysed by serious case reviews and inquiries into child deaths. Again, research suggests that providing professionals with tools to help them organise and critically appraise information in a systematic way can minimise bias and error and improve decision-making.

Structured decision-making (SDM) has been defined as a ‘general term for the carefully organized analysis of problems in order to reach decisions that are focused clearly on achieving fundamental objectives’. SDM draws both on decision theory and risk analyses and, in the field of child protection, has been described as ‘an example of an effort to integrate predictive (actuarial) and contextual assessment strategies’ [3]. So, for example, the Family Strengths and Needs Assessment (FSNA) is a structured approach to assessing (including scoring) child and family functioning in those domains recognised as important in child maltreatment - both from the point of view of causation (which actuarial tools do not address) and intervention. This aims to ensure a ‘logical fit’ between assessment and response.

The potential of structured approaches to improve assessment and decision-making has been reinforced by the findings of a systematic review of models of analysing significant harm, commissioned by the Department for Education (DfE) [4]. This review identified *two* SDM tools, both developed in the UK, which the review authors considered worth evaluating. Both address the three domains of the statutory guidance provided to professionals (known colloquially as ‘the Assessment Framework’) [5], namely, the child’s development needs; family and environmental factors, and parenting capacity.

The review authors note that both provide practitioners ‘with clear guidance about what to assess, and how to analyse and ‘make sense of’ the data collected’ (p.73). In relation to ‘Case Planning’, they note that only one of these - the Safeguarding Children Assessment and Analysis Framework (SAAF) - includes an assessment of the possibilities for future change (p.75). Based on this review, and evidence from the Munro report, the DfE commissioned this randomised trial of the effectiveness of the SAAF, alongside an implementation evaluation. Interventions such as SAAF are complex interventions, enacted in the complex environments of local authority (LA) Children’s Services Departments (CSDs). Understanding the process of implementation will inform the interpretation of the results of the trial and provide valuable learning to inform future use and roll-out.

### Safeguarding assessments

The work of social workers in CSDs is governed by legal statute. Section (S)17 of the Children Act 1989 lays upon them a ‘general duty … to safeguard and promote the welfare of children within their area who are in need’. Children are defined as being ‘in need’ when:(they are) ‘unlikely to achieve or maintain, or to have the opportunity of achieving or maintaining, a reasonable standard of health or development without the provision … of services by a local authority …’;(their) health or development is likely or be significantly impaired, or further impaired, without the provision of such services; or(they) are disabled

Children in need include children in need of protection, but S47 of the same Act lays down a specific duty to ‘make enquiries’ in respect of any child where there is ‘reasonable cause to suspect that … (he or she) … is suffering, or is likely to suffer, significant harm’. It is therefore commonplace to categorise referrals as either S17 (child in need) or S47 referrals.

Enquiries made under S47 are typically those where specific concerns have been raised about a child’s safety. However, a significant percentage of S17 cases may also raise concerns about a child’s development that are attributable to inadequate parenting and where assessment of family functioning is complex. For the purposes of this study, the impact of SAAF will be assessed with regard to complex assessments in both S17 and S47 cases.

### Aims of the study

#### Primary aim

The primary aim of this study is to determine whether complex assessments undertaken under S47 or S17 of the Children Act 1989 by social workers using SAAF, result in children being less likely to experience maltreatment or re-abuse than children whose social workers do not use SAAF.

It is hypothesised that social workers using SAAF will make more accurate assessments of risk and better child protection plans, including whether or not to remove a child from the care of his or her parents and the identification of effective intervention and protection plans to ensure their safety.

For the purposes of this study, complex assessments are those that require information to be gathered from a variety of sources in order to understand what is happening within a family, and where there are concerns about the adequacy of parenting, and/or whether a child has suffered, or is at risk of suffering, significant harm. Typically these assessments are referred to as ‘core assessments^a^’ or ‘comprehensive assessments’, although this language is now likely to change in the light of changes to guidance (see above).

#### Secondary aims

The secondary aims of the study are to determine the extent to which SAAF:

 improves the quality of social work assessments of harm, future risk and parents’ capacity for change is acceptable to social workers and other key stakeholders

If the data permit, the study will also seek to explore SAAF’s reliability in producing comparable assessment results across similar cases.

We will also seek to identify those implementation factors that hinder or facilitate its use and the reasons underpinning any adaptations made by individuals or teams.

### Study design

A multi-site, cluster-randomised controlled trial (RCT) in which teams of child protection social workers, stratified by site, are randomly allocated to one of two arms:i.)SAAF training followed by implementation of SAAF in S47 cases and complex S17 cases;ii.)Management as usual in S47 cases and complex S17 cases.

An implementation evaluation will run concurrently with the trial to explore the experience of using the SAAF, how it is integrated into working processes, and the barriers and facilitators to successful intervention. The study will also explore participant social workers’ experience of taking part in the trial.

## Methods

### Study sites

Six CSDs in England have been recruited by the DfE (Leeds, Oldham, Nottinghamshire, Greenwich, Bournemouth and Hampshire). These represent different CSD types (unitary, county, and metropolitan) located in a range of geographical areas (North West, Yorkshire and Humber, East Midlands, South East, South West and London).

### Eligibility criteria

#### Children’s services departments

##### Inclusion

CSDs in England were eligible for the study if they were willing to make relevant teams available to be randomised, willing to make staff in the experimental group available for training, and willing to require all participating social workers to comply with the study’s data requirements.

##### Exclusion

CSDs were not eligible if one or more of the following pertained: there were concerns about performance (for example, special measures, other DfE involvement), a major reorganisation was planned, the CSD was already using another risk assessment tool (for example, Graded Care Profile or Signs of Safety), the CSD had received training in recent years from the providers of the intervention, namely *Child and Family Training*.

#### Social work teams

Eligible teams within each CSD will be those that - between them - deal with the majority of complex S17 and S47 cases. Social workers in these teams are eligible, irrespective of experience or whether they are employees or agency staff. Generally, this will exclude teams that are working with looked-after children, court-work teams (where decisions have already been made that the level of risk posed to children justified their removal from parents’ care), intake teams or Multi-Agency Safeguarding Hub (MASH) teams (‘single point of entry’ teams who largely act as conduits to other teams’ services).

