### Study timeline

The trial formally commenced on 2 January 2014 (contract agreed). Recruitment by the DfE took place between December 2013 and April 2014.Following a study briefing session, social work teams in each of the participating CSDs will be randomised between May and August 2014. Social workers in the experimental arm in each CSD will receive training in SAAF in groups of 20. Once training is complete in a CSD, all social workers in that CSD will be required to provide information on each of the assessments they complete for a period of 6 months. The flow of work is not always predictable, and this period may be extended in order to obtain the necessary number of cases needed, or foreshortened in the even that this target is reached sooner. Figure 1 provides details of the timeline for each participating CSD.

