### Assignment of interventions

*Sequence generation*: social work teams within participating LAs will be randomly allocated to one of the two study arms. The allocation will be achieved by computer generated random numbers by the Northern Ireland Clinical Trials Unit (NI CTU) using randomly permuted blocks.*Allocation concealment*: the NI CTU will inform the PI and Trial Manager of the allocation of each social work team. The Trial Manager will then Email the designated contact person in each CSD to inform them of their allocation.The Trial Manager will also inform Children and Family Training, who will then liaise directly with the CSD to arrange training for those social workers/teams in the experimental arm.*Implementation*: the allocation to the intervention or control arm will be generated by the NI CTU and conveyed securely to the Trial Manager and PI.*Check on baseline equivalence*: all social workers will complete a baseline questionnaire prior to randomisation, which will provide information on their experience, training to date, expectations of the training, attitudes towards the trial, and so on. This will provide some indication of baseline equivalence between the two arms, as well as informing the interpretation of the study results.*Blinding*: given the nature of the intervention, the data to be collected, and the interface with the Trial Manager (who will be the point of contact for enquiries regarding data collection), it will not be possible to maintain the concealment of allocation, that is social workers will know whether or not they have been trained. Further, the Case Report Form will include questions about the use of the SDM tools (which the control group social workers will not be using) and the assessments that will be quality assessed may include indications that the authors were in receipt of training/used the SAAF SDM tools.

However, we will endeavour to select assessments for audit without divulging the arm from which they were sourced to those conducting the quality assessment. Each CSD will be asked to provide between 25 and 40 assessments, randomly selected by the NI CTU, from participating social workers in each arm, and make these available to the researchers undertaking the quality audit, without divulging which teams the authors belong to.

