### Data analysis

#### Assessing trial validity

Initial data analysis (descriptive statistics and bivariate tests) will examine the extent to which the necessary conditions required to permit a valid test of the efficacy of SAAF have been met [11]. This will include assessment of the achieved statistical power, patterns of attrition (social workers leaving/moving), between-group equivalence on key factors (for example, staff turnover, team size, experience of social workers, types of cases), SAAF fidelity (the extent to which SAAF appears to have been used as intended) and discriminability (for example, the approach to assessment undertaken by control social workers is sufficiently distinct).

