#### Assessing the effectiveness of SAAF

##### Intention-to-treat analyses

The primary outcome analysis will be an intention-to-treat analysis (ITT) such that all cases will be assessed in accordance with the randomisation. Analysis will be conducted both within and across LAs. We will maximise use of administrative data in order to document the extent of differences between the experimental and control groups.

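### Cases reach the arms by routing after team allocation is open, so case mix could differ between arms; the primary model should adjust for referral-time characteristics and fix each case's arm at first routing

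*Protocol article*

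**What the plan says.** - **Where the arms sit.** Under Study design, "teams of child protection social workers, stratified by site, are randomly allocated to one of two arms"; under Assignment of interventions, "social work teams within participating LAs will be randomly allocated to one of the two study arms". SAAF and control teams therefore work in the same department.
- **Who passes cases on.** Under Social work teams, the groups generally excluded include "intake teams or Multi-Agency Safeguarding Hub (MASH) teams (‘single point of entry’ teams who largely act as conduits to other teams’ services".
- **Who knows the allocation.** Under Assignment of interventions, "The Trial Manager will then Email the designated contact person in each CSD to inform them of their allocation". No limit on passing this on is described. The same section concedes that "it will not be possible to maintain the concealment of allocation, that is social workers will know whether or not they have been trained".
- **Order of events.** Under Study timeline, teams are randomised between May and August 2014, and case data come later: "Once training is complete in a CSD, all social workers in that CSD will be required to provide information on each of the assessments".
- **Analysis.** Under Intention-to-treat analyses, "all cases will be assessed in accordance with the randomisation". Under Assessing trial validity, arms are compared descriptively on "between-group equivalence on key factors (for example, staff turnover, team size, experience of social workers, types of cases". Inclusion of covariates adds regression models to the standard intention-to-treat (ITT) analysis, naming type of abuse and identified risk factors as examples. Multilevel models adds multilevel logistic models for cases within teams and an ancillary analysis by severity of the initial maltreatment.
- **Source of case detail.** Under Primary outcome, the Case Report Form is completed by the social worker straight after the assessment.

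**The concern.** Concealment is described for teams, but the analysed units are cases. A case acquires its arm when it is routed to a team, after that team's status is open inside the department. This is the usual route to identification bias in a cluster trial: randomising teams balances teams, and says nothing about which cases later reach them.

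If entry-point staff have discretion, they could send harder cases to teams trained in complex assessment, or spare those teams while they learn the tool. The first would mask a benefit and the second would imitate one. ITT by team keeps the team comparison intact but does not make the cases exchangeable.

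The planned covariate adjustment is weaker than it looks if its variables come from the Case Report Form. Those fields are completed after assessment by workers who know their arm, and SAAF is meant to change how risk is identified. Adjusting for them could absorb part of a real effect or leave confounding in place.

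The arm of a case that moves is also open. The article expects children to pass between S17 and S47, and notes that one case may have two recorded assessments. It does not say which team's arm such a case carries.

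**Working it through.** **1. The plan's own figure.** Table 1, scenario 3b: 10% v 5%, unclustered total 900, design effect 2.0, so 900 × 2.0 = 1,800. Effective size per arm = 1,800 / 2.0 / 2 = 450. Alpha is not stated; I assume 0.05 two-sided.

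Power = Φ[(d − 1.96·SE0)/SE1], where SE0 = √(p̄(1−p̄)·2/n) and SE1 = √((p1(1−p1) + p2(1−p2))/n).

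For 10% v 5%: SE0 = √(0.075 × 0.925 × 2/450) = 0.01756; SE1 = √((0.0900 + 0.0475)/450) = 0.01748; (0.0500 − 0.0344)/0.01748 = 0.89; power 81.4%.

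**2. Adding a case-mix shift (assumptions, not in the article).** One third of cases are high-risk at 20% and two thirds low-risk at 5%, so the mean is 20/3 + 10/3 = 10%. SAAF halves both. The high-risk share is δ higher in SAAF teams, split evenly around one third. There is no covariate adjustment, and the net shift runs one way across all CSDs.

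For δ = 0.10:
- Control: 10% − 0.05 × 15 points = 9.25%.
- SAAF: 0.5 × (10% + 0.05 × 15 points) = 5.375%.
- d = 3.875 points, SE0 = 0.01736, SE1 = 0.01731; (0.03875 − 0.03402)/0.01731 = 0.27; power 60.8%.
- With no SAAF effect, the spurious difference is 0.10 × 15 = 1.5 points.

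**3. Range over assumptions.**

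| Assumed strata (mean 10%) | Shift (points) | Power if SAAF halves risk | Spurious difference if no effect | Type I error |
|---|---|---|---|---|
| 1/3 at 20%, 2/3 at 5% | 5 | 72.0% | 0.75 | 6.6% |
| same | 10 | 60.8% | 1.5 | 11.6% |
| same | 20 | 36.1% | 3.0 | 32.3% |
| 1/3 at 15%, 2/3 at 7.5% | 10 | 72.0% | 0.75 | 6.6% |
| same | 20 | 60.8% | 1.5 | 11.6% |
| half at 15%, half at 5% | 10 | 68.5% | 1.0 | 7.9% |
| same | 20 | 52.6% | 2.0 | 17.0% |
| half at 18%, half at 2% | 10 | 59.2% | 1.6 | 12.6% |
| same | 20 | 32.9% | 3.2 | 35.9% |

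**4. Opposing shifts.** With the first set of strata, if four of six equal-sized CSDs shift by 10 points one way and two the other, the net shift is (4 × 10 − 2 × 10)/6 = 3.3 points. Power is then about 75% and the spurious difference 0.5 points.

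**The case against.** Several points on the other side stand.

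- **Knowledge of allocation.** A reader might infer that entry-point staff know each case's arm with certainty. The article says only that a designated contact in each CSD is told, and its remark on lost concealment is about social workers knowing whether they were trained. Knowable is as far as the text goes.
- **Discretion.** A reader might infer that one entry point feeds both arms in every CSD and can choose between them. The exclusion is worded as general, and no routing rule is given. Routing by area or rota would leave little room to steer. The article also leans towards stable practice: SAAF does not replace existing policies, controls follow departmental policy, and CSDs planning major reorganisation were excluded. None of this binds routing.
- **Existing safeguards.** It would be wrong to call the descriptive check the only protection, since case-mix covariate models are planned. They remain after-the-event remedies, additional to the standard ITT.
- **Motive.** Nothing says CSDs paid for the training; the Department for Education commissioned the trial.
- **Transferred cases.** The article does not say a case is counted under its final team. It is silent, and a fuller protocol or analysis plan may settle this. Such a plan could define the arm, but could not restore balance once cases had been routed.
- **Size.** The calculations rest on assumed strata and a net one-way, unadjusted shift.

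**Conclusion.** The concern holds as an exposure to bias. Three features are documented: both arms within each CSD, entry-point teams generally outside the randomisation, and case collection only after allocation and training. Together they allow case mix to differ between arms if routing is discretionary. The article does not show that steering happened or that routing staff were told the allocation, and it should not be read that way.

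The size cannot be estimated from the article. On the assumptions above, a net 10-point imbalance costs roughly 9 to 22 points of power, or gives a spurious difference of 0.75 to 1.6 points against a target difference of 5. Opposing shifts between CSDs, or sound adjustment, would make it smaller. Because the main remedy is nearly free, the change is worth making even though the risk is only potential.

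**What to change.** 1. **Intention-to-treat analyses and Inclusion of covariates:** adjust the primary model for characteristics fixed before assessment and held in CSD administrative data, namely previous CPP and previous referrals, taken as they stood at first routing. Do not rely on post-assessment Case Report Form fields for case-mix adjustment.
2. **Intention-to-treat analyses:** define a case's arm as that of the participating team to which the referral was first routed, and keep it if the case, or a later S17 or S47 assessment, moves.
3. **Assessing trial validity:** compare arms on referral-time fields: referral source, referral reason, previous CPP and previous referrals.
4. **Routing:** ask CSDs to keep whatever routing rule they already use during collection and to log departures with reasons. Make this a request, not a new condition of participation, because CSDs have already consented and all teams are randomised. At publication, collection had begun in only one of the six CSDs, so the request could still help in the other five.

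Cost: a few extra fields in an extract the trial already takes, some wording, a log for CSDs to keep, and slight dilution of the effect when cases transfer. No extra cases are needed. Items 1 to 3 should be fixed before outcomes are compared by arm.
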